## **6.2 Methods of minimising bias**

### **6.2.1 Randomisation**

Patients will be assigned to their respective group using a computer-generated randomization list by [www.randomisation.com](http://www.randomisation.com). Randomisation will be stratified according to BMI in three groups: <25, 25-30 and >30 and smoker status (non-smoker, non-daily smokers and daily smokers < 40 years of age, daily smoker > 40 years of age).

Allocated group will be kept in sealed opaque envelopes opened after induction of anaesthesia when proper face-mask ventilation is confirmed. Patients excluded from the study before opening of the randomisation envelope (e.g. because of impossible mask ventilation) will be replaced as if not eligible for the study.

### **6.2.2 Blinding procedures**

Patients are under general anaesthesia therefore blinded to the treatment group, but due to the different oxygen delivery systems study personnel in the operating theatre cannot be blinded.

## **6.3 Unblinding Procedures (Code break)**

Not needed, as this will be an open study.

## **7. STUDY POPULATION**

### **7.1 Eligibility criteria**

We will include consenting adult patients ( $\geq 18$  years) undergoing elective surgery that requires general anaesthesia at the University Hospital Inselspital in Bern, ASA physical status 1-3 and written informed consent in German.

Exclusion criteria are:

- Any Indication for fibre optic intubation
- Expected impossible mask ventilation
- Known coronary heart disease
- Known heart failure, NYHA classification  $\geq 2$
- Arrhythmias in need of anti-arrhythmic therapy (e.g. implanted cardio defibrillator)
- Peripheral occlusive arterial disease, Fontaine  $\geq 2b$
- Known stenosis of the (common or internal) carotid or vertebral arteries
- Treatment with beta-receptor antagonists
- BMI  $> 35\text{kg/m}^2$  and BMI  $< 16\text{kg/m}^2$
- Hyperkalaemia ( $K > 5.5 \text{ mmol/l}$ )
- Known COPD Gold classification  $\geq 2$
- Known pulmonary arterial hypertension, systolic  $> 35\text{mmHg}$
- Known obstructive sleep apnoea syndrome in need of therapy
- High risk of aspiration (requiring rapid sequence induction intubation)

- Increased intracranial pressure
- Intracranial surgery
- Limited knowledge of German language
- Absent power of judgement
- Anaemia, Hb < 100 g/l
- Pregnancy (pregnancy test in all female patients)
- Neuromuscular disorder
- Known or suspected cervical spine instability
- Nasal obstruction, impossibility of nasal ventilation (both sides patent)
- Allergies or contra-indications to one or more of the used anaesthesia agents

## 7.2 Recruitment and screening

Patients are screened during the pre-anaesthesia visit before surgery. Eligible patients will be asked if they might participate in the study during the pre-anaesthesia visit and they will sign the informed consent. For female participants, we will additionally measure  $\beta$ -HCG in the blood as part of the standard preoperative laboratory control, to rule out pregnancy.

## 7.3 Assignment to study groups

Patients will be randomly assigned to their respective group using a randomization out of [www.randomisation.com](http://www.randomisation.com). Randomization will be stratified according to BMI (16-25kg/m^2, 25-30 kg/m^2, 30-35 kg/m^2), smoker status (non-smoker, non-daily smoker, daily smoker) and age (18-40 years, > 40 years).

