| 
Inclusion /
Exclusion criteria:
 | 
We will include adult patients undergoing general anaesthesia for elective surgery at the Dept. of Anaesthesiology and Pain Therapy, Bern University Hospital, Inselspital, Bern, ASA physical health status 1-3, who have provided written informed consent in German.
 
Exclusion criteria are:
 
 
• Any Indication for fibre optic intubation
 
• Expected impossible mask ventilation
 
• Known coronary heart disease
 
• Known heart failure, NYHA classification <math>\geq 2</math>
 
• Arrhythmias in need of anti-arrhythmic therapy (e.g. implanted cardio defibrillator)
 
• Peripheral occlusive arterial disease, Fontaine <math>\geq 2b</math>
 
• Treatment with beta-receptor antagonists
 
• Known stenosis of the (common or internal) carotid or vertebral arteries
 
• BMI <math>> 35\text{kg/m}^2</math> and BMI <math>< 16\text{kg/m}^2</math>
 
• Hyperkalaemia (K <math>> 5.5\text{ mmol/l}</math>)
 
• Known COPD Gold classification <math>\geq 2</math>
 
• Known pulmonary arterial hypertension, systolic <math>> 35\text{mmHg}</math>
 
• Known obstructive sleep apnoea syndrome in need of therapy
 
• High risk of aspiration (requiring rapid sequence induction intubation)
 
• Increased intracranial pressure
 
• Intracranial surgery
 
• Limited knowledge of German language
 
• Absent power of judgement
 
• Anaemia, Hb <math>< 100\text{ g/l}</math>
 
• Pregnancy (pregnancy test in all female patients prior to anaesthesia)
 
• Neuromuscular disorder
 
• Known or suspected cervical spine instability
 
• Nasal obstruction, impossibility of nasal ventilation (both sides patent)
 
• Allergies or contra-indications to one or more of the used anaesthesia agents
 
 
Randomization will be stratified according to BMI (16-25kg/m^2, 25-30 kg/m^2, 30-35 kg/m^2), and smoker status (non-smoker, non-daily smoker, daily smoker <math>< 40</math> years of age, daily smoker <math>> 40</math> years of age).
 |

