### **2.1.3 The methodology is ethically appropriate to gain new generalizable knowledge**

The patients are blinded to the randomisation. The responsible anaesthetist cannot influence the apnoea time (very low risk of creating bias). The four groups will be stratified according to BMI (16-25kg/m^2, 25-30 kg/m^2, 30-35 kg/m^2), smoker status (non-smoker, non-daily smoker, daily smoker) and age (18-40 years, > 40 years) in order to maintain statistical equality. The trial method is well suited to study the research question and the participating anaesthetists are comfortable and used to all four oxygenation possibilities. All patients that could be harmed through high levels of  $\text{CO}_2$  or desaturation are excluded from the study. The study group has a wide experience with HFNCT and has performed a similar study in children before (Riva et al, BJA, 2018, in press).

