### 10.2 Determination of Sample Size

We assumed that with maximal flow of 70L O2/min and maximal mouth opening, there would be the least increase of  $p_{tc}CO_2$ /min. Patel et al. showed an increase of only 1.13mmHg using this technique [2]. However, this was  $etCO_2$  instead of  $p_{tc}CO_2$ . According to Gustafson et al., who measured  $p_{tc}CO_2$  as well as  $p_aCO_2$ , the  $CO_2$  increase was in fact 1.8mmHg/min, with a standard deviation of 0.35mmHg [3]. This correlated very well with our own findings in our pilot study (not published).

Using a non-inferiority design, a difference of means of 0.3mmHg/min, a standard deviation of 0.35mmHg/min, an alpha of 0.025 (one-sided) and a power of 80%, the necessary sample

size calculates to 22 patients per group. Therefore, we will include 25 patients in each group to account for possible drop outs. A value of 0.3mmHg/min would still only result in a difference in increase of 9mmHg in 30 minutes of apnoea time. We defined this as measurable, but still clinically acceptable, because the normal range of standard arterial pCO2 is 11mmHg (35-46 mmHg) [6].

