### **10.3 Planned Analyses**

#### **10.3.1 Datasets to be analysed, analysis populations**

Distribution of data will be checked using qq-plots and swilk command in stata, normal distributed data will be presented as means and standard deviation, otherwise median and interquartile range will be used. Proportions will be presented as numbers and percentage. Analytical statistics uses Mann-Whitney u-tests and Students t-test, according distribution, or ANOVA and Kruskal-Wallis for multiple groups. Each of the groups will a-priori be compared to the control group independently, without correction of multiple comparisons. Other multiple comparisons or subgroup-analyses will be performed using correction factors. Proportions will be compared by Chi-square tests or Fisher's exact test. As sensitivity analyses, we will do regression analyses, using mixed effects linear regressions.

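### The stratification scheme is defined in incompatible ways (18 cells versus 12 or 9), and the primary test leaves the stratification factors out, which costs power if they are prognostic

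*Protocol*

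**What the plan says.** The protocol describes the strata in four places.

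- **Section 7.3:** three BMI bands (16-25, 25-30, 30-35), with "smoker status (non-smoker, non-daily smoker, daily smoker) and age (18-40 years, > 40 years".
- **Section 2.1.3:** the same BMI bands, with "smoker status (non-smoker, non-daily smoker, daily smoker) and age (18-40 years, > 40 years) in order to maintain statistical equality".
- **Synopsis (inclusion/exclusion row):** the same BMI bands, "and smoker status (non-smoker, non-daily smoker, daily smoker", with the daily smokers then divided into those under 40 and those over 40. Age is not a factor for anyone else.
- **Section 6.2.1:** BMI below 25, 25-30 and above 30, with "smoker status (non-smoker, non-daily smokers and daily smokers < 40 years of age, daily smoker > 40 years of age".

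For the analysis, section 10.3.1 says "Analytical statistics uses Mann-Whitney u-tests and Students t-test, according distribution, or ANOVA and Kruskal-Wallis for multiple groups". Each group is compared with control separately, and no stratification factor is named. It adds "As sensitivity analyses, we will do regression analyses, using mixed effects linear regressions", without naming covariates. The statistical considerations in the synopsis repeat this text.

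Section 10.2 sizes the trial with "a difference of means of 0.3mmHg/min, a standard deviation of 0.35mmHg/min" and "an alpha of 0.025 (one-sided) and a power of 80"%, which gives 22 per group, raised to 25.

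**The concern.** Randomisation uses one list and one set of sealed envelopes, so there can be only one set of strata. Under sections 7.3 and 2.1.3, a non-smoker aged 30 and one aged 60 are in different strata. Under the synopsis and section 6.2.1 they are in the same one. A reader cannot tell which list was generated, or whether age was balanced outside the daily smokers.

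Stratified randomisation also makes the arms more alike on the stratified factors than chance would. If those factors predict the CO2 slope, the treatment difference varies less than an unadjusted standard error assumes. Leaving the factors out gives up precision that the design has already bought, in a trial with only three spare patients per arm.

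**Working it through.** **1. The plan's own figure.** With true difference 0 (assumed; section 10.1 reports no differences in the pilot), margin 0.3, SD 0.35, one-sided alpha 0.025 and power 80%:

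n = 2 × (1.960 + 0.842)² × (0.35/0.3)² = 2 × 7.85 × 1.361 = 21.4, so 22 per group.

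The stated 22 is reproduced. Exact (noncentral t) power is 79.3% at 22 per arm and 84.4% at 25.

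**2. Cells implied by each description, for 100 patients in four arms.**

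| Source | Levels | Cells | Patients per cell | Per arm per cell |
|---|---|---|---|---|
| 7.3 and 2.1.3 | 3 × 3 × 2 | 18 | 5.6 | 1.4 |
| Synopsis | 3 × 4 | 12 | 8.3 | 2.1 |
| 6.2.1, young daily smokers separate | 3 × 4 | 12 | 8.3 | 2.1 |
| 6.2.1 as punctuated | 3 × 3 | 9 | 11.1 | 2.8 |

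**3. Boundaries.** BMI 25 and BMI 30 each fall in two bands in the synopsis, 2.1.3 and 7.3; section 6.2.1 is clear on both. A daily smoker aged exactly 40 has no cell in the synopsis or 6.2.1; 2.1.3 and 7.3 do place age 40. No single section is free of a boundary fault.

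**4. Effect of omitting the factors.** Let R² be the share of slope variance explained by the strata. The protocol gives no value, so 0 to 30% is an assumed range. Block size is not stated either; 4 is assumed.

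- *Error rate.* With near-perfect balance, the unadjusted test's true one-sided error is 1 − Φ(1.96/√(1 − R²)), which is 1.9/1.4/1.0% at R² = 10/20/30%. Simulated stratified blocks give about 1.8/1.5/0.7-1.1%. At R² = 0 it is close to the nominal 2.5%.
- *Standard error.* At R² = 30%, 18 cells and 25 per arm, the mean unadjusted standard error is 0.099 while the estimate's true SD is 0.084. Since 0.099/0.084 = 1.18, intervals are about 18% too wide.
- *Adjusted power at 22 per arm.* The residual SD becomes 0.35 × √(1 − R²) = 0.332/0.313/0.293. Noncentrality is 0.3/(SD × √(2/22)) = 3.00/3.18/3.40, and power is about 83/87/91%.
- *Unadjusted power at 22 per arm.* This rises too, because balance also steadies the unadjusted estimate. Simulation gives about 80/81/82%.

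| R² (assumed) | True one-sided error, unadjusted | Power unadjusted, n = 22 | Power adjusted, n = 22 | Gain (points) |
|---|---|---|---|---|
| 0 | about 2.5% | 79% | about the same | 0 |
| 10% | 1.8% | 80% | 83% | 3 |
| 20% | 1.5% | 81% | 87% | 6-7 |
| 30% | 0.7-1.1% | 82% | 91% | 9 |

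At 25 per arm with no drop-out, simulated power is 0.83-0.84 unadjusted against 0.82-0.84 adjusted at R² = 0, and 0.86-0.88 against 0.94-0.95 at R² = 30%. Adjusted one-sided error stays at about 2.1-2.7%.

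**5. Does the finer scheme balance worse?** SD of the imbalance in a combined prognostic score between two arms (assumed case mix):

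| Block size | No strata | 9 cells | 12 cells | 18 cells |
|---|---|---|---|---|
| 4 | 0.286 | 0.174 | 0.179 | 0.124 |
| 8 | 0.281 | 0.196 | 0.201 | 0.162 |

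The 18-cell scheme balances best at both block sizes. Its cost is some drift in arm size: the central 95% range with 18 cells is 22-28 with blocks of 4 and 21-29 with blocks of 8.

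**The case against.** The strongest reply is that nothing here invalidates the trial. The unadjusted test errs only towards caution, and only if the strata are prognostic. The protocol justifies stratifying by a wish for comparable groups and does not claim that BMI, smoking or age predict the CO2 slope. Regression is already planned as a sensitivity analysis, and its covariates could properly be set in a statistical analysis plan. The boundary faults are small, and each is settled in at least one section. All of this stands and limits the size of the point. It does not remove it: the schemes still conflict, and section 10.3.1 itself chooses unadjusted tests as the main comparison, so this is not a gap left for a later document.

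Four stronger readings are tempting but not supported.

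- *Eighteen sparse cells dilute balance, so stratification does little.* Step 5 shows the opposite for blocks of 4 or 8. The claim would also undercut the standard-error point, which depends on the strata balancing well.
- *The error bars favour non-inferiority.* They are too wide, not too narrow.
- *Adjustment gains 4/8/12 points over 79%.* That baseline is the R² = 0 figure; the like-for-like gain is 3/6-7/9 points.
- *Uneven arms undermine the sample size.* The drift depends on an unstated block size, and power is 77% at 21 per arm against 79% at 22.

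**Conclusion.** The point holds in two parts.

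The textual contradiction needs no assumptions: 18 cells in two places, 12 or 9 in two others, with overlapping or missing boundaries. By itself it does not bias the treatment comparison. It leaves the implemented design unknown and boundary patients without a defined stratum.

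The analysis part is a conditional loss of efficiency. If the strata explain 10-30% of the slope variance, the unadjusted test gives up roughly 3 to 9 points of power at 22 per arm and runs well below its nominal error. If they explain nothing, there is no loss either way. The figures rest on assumed R², assumed blocks of 4, a true difference of 0, and simulation error of a few tenths of a point in the error rates. This is worth correcting because the correction is nearly free, not because the planned test would mislead.

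**What to change.** 1. State one stratification scheme, identically worded, in the synopsis and sections 2.1.3, 6.2.1 and 7.3. If a list has already been generated, describe that list. If not, the 12-cell synopsis scheme is workable. Close the boundaries, for example BMI below 25, 25 to below 30, and 30 or above; daily smokers below 40, and 40 or above.
2. In section 10.3.1 and the synopsis, take the primary estimate from one linear model on all four arms, with treatment and the stratification factors as main effects. Report each comparison with control as a two-sided 95% confidence interval against 0.3 mmHg/min. Keep the unadjusted difference as a sensitivity analysis.

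The cost is protocol wording and one model statement. Main effects use 5 degrees of freedom under the 12-cell scheme (2 + 3) or the 18-cell scheme (2 + 2 + 1), out of 100 − 4 = 96. The sample size does not change.

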## 7.4 Criteria for withdrawal / discontinuation of participants

The study will be stopped if change of anaesthesia procedure (i.e. no general anaesthesia necessary) will be decided. Impossible mask ventilation before apnoea or any malfunction of necessary equipment (e.g. transcutaneous CO2 measurement) will also terminate the study.

# 8. STUDY INTERVENTION

## 8.1 Identity of Investigational treatment

### 8.1.1 Experimental Intervention

The **first** group receives high-flow nasal cannula therapy with 70 l/min with 100% oxygen via OptiFlow™ by Fisher&Paykel™, Auckland, NewZealand, using jaw thrust.

The **second** group receives 10 l/min of 100% humidified oxygen using Carbamed digiflow, Aquapak Hudson RCI and nasal cannula

**Third** group receives low-flow 2l/min of 100% humidified oxygen using Carbamed digiflow, Aquapak Hudson RCI and nasal cannula.

### 8.1.2 Control Intervention (routine treatment)

**Control** group: High-flow nasal cannula therapy with 70 l/min with 100% oxygen via OptiFlow™ by Fisher&Paykel™, Auckland, NewZealand performing continuous laryngoscopy (standard of care), with a MacGrath™ MAC videolaryngoscope, Medtronic, Dublin, Ireland.

## **8.2 Administration of experimental and control interventions**

### **8.2.1 Experimental Intervention**

After apnoea sets in and mask ventilation is successfully established, randomization envelopes are opened and according to group allocation, one of the following oxygen delivery systems is applied.

The first group receives high-flow nasal cannula therapy with 70 l/min with 100% oxygen via OptiFlow™ by Fisher&Paykel™, Auckland, NewZealand, using jaw thrust.

The second group receives 10 l/min of 100% humidified oxygen using Carbamed digiflow, Aquapak Hudson RCI and nasal cannula

Third group receives low-flow 2l/min of 100% humidified oxygen using Carbamed digiflow, Aquapak Hudson RCI and nasal cannula.

### **8.2.2 Control Intervention**

Control group: High-flow nasal cannula therapy with 70 l/min with 100% oxygen via OptiFlow™ by Fisher&Paykel™, Auckland, NewZealand performing continuous laryngoscopy (standard of care), with a MacGrath™ MAC videolaryngoscope, Medtronic, Dublin, Ireland.

## **8.3 Data Collection and Follow-up for withdrawn participants**

No further data collection after withdrawal, already collected data will be analyzed and after data evaluation anonymised. These patients will be visited after anaesthesia anyhow to ensure wellbeing.

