According to randomization, the intervention will be applied. If jaw thrust is performed, upper airway patency will be visually confirmed using nasopharyngeal fiberscope (EF-N slim, Acutronic, Hirzel, Switzerland). In most cases this should be the case [18]. If not, an oropharyngeal airway (Guedel) will be inserted, and if necessary, manual assistance performed to obtain the required result. If, despite these interventions, the airway is not patent, the study will end prematurely (drop-out). This is very unlikely to happen.

After confirmation of upper airway patency, the experiment will be continued until one of the following criteria is met: SpO2 < 92%, ptcCO2 > 80 mmHg, pH < 7.1, K > 6.0 mmol/l or apnoea-time > 15 minutes.

During the intervention, we will continuously measure arterial blood pressure, pulse oximetry, ptcCO2, ptcO2, heart rate, depth of anaesthesia (Narcotrend™), brain oxygenation, cardiac output by pulse contour analysis, and ventilation distribution changes by thoracic electrical impedance tomography (EIT). Latter will be measured with a PulmoVista® 500, by Dräger, Lübeck, Germany. Furthermore, we will take arterial blood samples at the onset of apnoea, one minute after apnoea, and thereafter every two minutes to perform blood gas analysis (total of max. 10 measurements).

During the experiment, one anaesthesia staff member will be free of all study related responsibilities in order to ensure the patient's wellbeing during anaesthesia consisting of stable blood pressure, neuromuscular blockage, and anaesthesia depth.

The experiment stops, if one of the following criteria is met: SpO2<92%, ptcCO2>80 mmHg, pH<7.1, K>6.0 mmol/l, t >15 minutes. Thereafter the airway will be secured in the planned manner and anaesthesia will continue without any further interruptions.

Patients will be visited before discharge on the first postoperative day or contacted by phone, and asked for any sort of pain (throat, mandibular joint, head, etc.), nausea, vomiting, nasal dryness, lip injuries, dental damages, other injuries, or any other discomfort or complication using a (modified) visual analogue scale (VAS), where 0 is no pain (or discomfort), and 10 is maximum pain (or discomfort) where applicable. We will also assess all kinds of injuries obtained during anaesthesia.

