#### 8.5.3.1 Adverse events

Any adverse events during the study period will be recorded.

An **Adverse Event (AE)** is any untoward medical occurrence in a patient or a clinical investigation participant administered a pharmaceutical product, and which does not necessarily have a causal relationship with the study procedure. An AE can therefore be any unfavourable and unintended sign (including an abnormal laboratory finding), symptom, or disease temporally associated with the use of a medicinal (investigational) product, whether or not related to the medicinal (investigational) product. [ICH E6 1.2]

A **Serious Adverse Event (SAE)** is classified as any untoward medical occurrence that:

- results in death
- is life-threatening
- requires in-patient hospitalization or prolongation of existing hospitalisation
- results in persistent or significant disability/incapacity
- is a congenital anomaly/birth defect

In addition, important medical events that may not be immediately life-threatening or result in death, or require hospitalisation, but may jeopardise the patient or may require intervention to prevent one of the other outcomes listed above should also usually be considered serious. [ICH E2A].

All SAEs will be reported immediately and within a maximum of 24 hours to the Sponsor-Investigator of the study.

SAEs resulting in death are reported to the local Ethics Committee within 15 days.

SUSARs will be reported to the local Ethics Committee within 15 days.

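### Section 8.3 ends all data collection at withdrawal, with no exception for adverse events or the postoperative interview, and so conflicts with 8.5.3.1, whose recording period is undefined

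*Protocol*

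**What the plan says.** Section 8.3 of the protocol has two sentences. The first reads "No further data collection after withdrawal, already collected data will be analyzed and after data evaluation anonymised". The second reads "These patients will be visited after anaesthesia anyhow to ensure wellbeing". Neither mentions adverse events or the interview, and neither separates a participant who withdraws consent from one whose run the study team ends.

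The reasons for ending a run are elsewhere:

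- Section 7.4, headed as criteria for withdrawal or discontinuation, lists a change of anaesthesia procedure and then "Impossible mask ventilation before apnoea or any malfunction of necessary equipment", giving failure of the transcutaneous CO2 measurement as its example.
- Section 6.1 adds, after the steps taken to open the airway: "If, despite these interventions, the airway is not patent, the study will end prematurely (drop-out". It comments that "This is very unlikely to happen".
- Section 6.2.1 says that patients excluded before the envelope is opened "will be replaced as if not eligible for the study".

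On safety data, section 8.5.3.1 states "Any adverse events during the study period will be recorded" and requires all serious adverse events to reach the Sponsor-Investigator within 24 hours. Sections 6.1 and 8.6 describe a postoperative visit with a structured interview on sore throat, jaw pain, dental damage, oropharyngeal injury and similar harms. Section 10.3.2 compares side-effect incidences with published results.

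**The concern.** A patient dropped after the envelope is opened is randomised and has been exposed to study procedures. The arterial line is already in place. Depending on the arm and the moment of stopping, the patient may also have had nasopharyngoscopy, jaw thrust or laryngoscopy, an oropharyngeal airway, manual assistance and some apnoea. Section 3.6 itself names mucosal bleeding and arterial-catheter complications as risks.

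None of the reasons in 7.4 and 6.1 removes permission to record data. Yet a team that follows 8.3 literally would visit such a patient and enter nothing. Section 11.1.1 makes the CRF the source record, so a finding kept out of it may have no study record at all.

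At stake is the completeness of the safety description. Section 10.3.2 sets incidences against the literature and plans no comparison between arms, so nothing inside the trial would reveal an omission. The omission could also be uneven: 6.1 ties the patency check to jaw thrust, which only the three experimental groups receive, although the synopsis does not limit the check in this way.

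**Working it through.** **1. The only drop-out figure in the plan.** Section 10.2 uses a margin of 0.3 mmHg/min, an SD of 0.35 mmHg/min, one-sided alpha 0.025 and power 80%. With a true difference of zero,

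n = 2 × SD² × (1.960 + 0.842)² / margin² = 2 × 0.1225 × 7.85 / 0.09 = 21.4, rounded up to 22 per group.

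This reproduces the stated 22. The step to 25 leaves 25 − 22 = 3 per group, or 3/25 = 12%. The synopsis says that this step covers missing data as well as drop-outs, so it is not a count of patients who fall under 8.3.

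**2. Who falls under 8.3.**

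| How the run ends | Source | Randomised? | Affected by 8.3? |
|---|---|---|---|
| SpO2, ptcCO2, pH, potassium or time limit reached | Synopsis; 6.1 | Yes | No: a study end-point, follow-up continues |
| Mask ventilation impossible | 7.4; 6.2.1 | No: envelope unopened | No: replaced |
| Airway stays non-patent | 6.1 | Yes | Yes, if a drop-out counts as withdrawn |
| Equipment malfunction after the envelope is opened | 7.4 | Yes | Yes |
| Changed anaesthesia procedure after the envelope is opened | 7.4 | Yes | Yes, in principle |
| Consent withdrawn | 2.7 | Either | Yes, and reasonably so |

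**3. Does 8.5.3.1 settle the matter?** It depends on what the study period is. The synopsis and 8.5.1 use the term for the time of continuous monitoring in theatre.

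- If that meaning holds in 8.5.3.1, the postoperative visit lies outside it. Section 8.3 then governs, and the findings are not collected.
- If the period includes the visit, 8.5.3.1 requires recording and 8.3 forbids it.

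The text needs correcting on either reading. The 24-hour rule covers serious events only, whereas the interview looks mainly for non-serious airway harm.

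**4. Scale, on assumptions only.** The documents give neither a number of such drop-outs (k) nor a harm rate (p). The chance that at least one of k patients has a harm is 1 − (1 − p)^k:

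| Assumed k | p = 5% | p = 10% | p = 20% |
|---|---|---|---|
| 3 | 14% | 27% | 49% |
| 6 | 27% | 47% | 74% |

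For example, 1 − 0.9³ = 0.271.

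The effect on an overall incidence is smaller. Assume 5% among completers and 20% among drop-outs, with the recorded rate based on completers alone. With 3 drop-outs in 100, the full rate is (97 × 5% + 3 × 20%)/100 = 5.45%, against 5% recorded. With 6 it is (94 × 5% + 6 × 20%)/100 = 5.9%. If drop-outs have the same rate as completers, the recorded rate is unchanged and only events are lost.

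**The case against.** The strongest reply is that 8.5.3.1 already protects these patients. It covers any adverse event and every serious one, with no exemption for withdrawn participants, and 6.1 and 8.6 describe the visit and interview without exempting anyone. This stands in part. A reader might infer from 8.3 that harms are certainly seen and left unrecorded, or that a serious event found at the visit would be lost. The documents do not support that: serious events must be reported whatever 8.3 says, and for non-serious ones the protocol gives two instructions that are not reconciled.

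The wording on withdrawal is also open. Section 2.7 uses the word for consent, 6.1 speaks of a drop-out, and 7.4 of stopping the study. One could read 8.3 as meant for consent only. The heading of 7.4 does cover withdrawal, however, and 8.3 draws no distinction, so the literal reading remains available to site staff.

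Three further readings are tempting and should be set aside:

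- **Every failed run is affected.** Runs stopped for desaturation, hypercapnia, acidosis or hyperkalaemia have met an end-point and keep their follow-up.
- **Up to 12 of 100 patients lack safety data** (3 in each of 4 groups). The allowance is a cushion for the primary outcome and includes missing data. A patient can lack a usable ptcCO2 slope and still be interviewed.
- **Drop-outs had the most airway manipulation.** This may fit the non-patent airway, which the protocol thinks very unlikely. It does not fit a failed sensor, and early stopping shortens exposure compared with a run of up to 15 minutes.

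The consequences are also limited. The interview is not among the outcomes listed in 5.2 and 5.3, and data collected before withdrawal are kept and analysed.

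**Conclusion.** The point holds as an inconsistency with a modest safety consequence. Section 8.3 is an explicit rule, not a detail left to a later document. It cannot be followed together with 8.5.3.1 unless the study period stops before the postoperative visit, and in that case the visit's findings have no recording rule for these patients.

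The effect is confined to randomised patients whose run is ended after the envelope is opened for reasons other than consent or a study end-point. Their non-serious postoperative harms could be left out of the incidences used in 10.3.2. The number is probably small and the documents give no rate. On the assumptions shown, an overall incidence would shift by less than one percentage point, though single events could well be missed. The sample size and the primary analysis are unaffected.

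This rests on reading 8.3 literally and on counting the terminations in 7.4 and 6.1 as withdrawals. If the sponsor meant consent only, the correction is still needed, because the text does not say so.

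**What to change.** Make three changes of wording:

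1. In 8.3, limit the end of data collection to participants who withdraw consent for the use of their data.
2. In 8.3, state that every randomised patient whose run ends early under 7.4 or 6.1 keeps the adverse-event recording of 8.5.3.1 and the structured interview of 8.6, entered in the CRF and reported in the allocated arm.
3. In 8.5.3.1, define the adverse-event period so that it includes the postoperative visit.

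The visit already takes place, so the cost is an amendment to the text and a few extra interview forms to enter.
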